## **8 Ethical considerations**

### **8.1 Regulation statement**

The SMILE registry is classified as a non-WMO study and complies with the General Data Protection Regulation and the Dutch Civil Code (WGBO). Under Article 458 of the WGBO, patient data for scientific research without explicit consent is permitted when obtaining such consent is impractical or unreasonable, if patient privacy is safeguarded, and the research serves a legitimate public interest. The ethical framework for this registry has been reviewed and approved by the Medical Ethics Review Committee of Maastricht UMC+.

### **8.2 Recruitment and consent**

The SMILE registry operates under a no-objection system. Patients are eligible for inclusion when moderate-severe MR is observed on a cardiac echocardiogram. These eligible patients are informed about the study through communication via post or telephone, and they are provided with detailed information regarding the purpose and scope of the registry. Patients are explicitly allowed to object to the use of their data. If no objection is raised, their data will be included in the registry. This method ensures compliance with ethical principles while facilitating a comprehensive and unbiased collection of data necessary to evaluate and improve the quality of care for MR patients.

## **9 Administrative aspects, monitoring and publication**

### **9.1 Handling of storage and data documents**

The research data collected by the participating centres will be centrally managed by the research team at the MUMC+. The data will be securely saved, and only coded patient information will be used for data analysis. Access to the data will be restricted to the same research team and will be utilized exclusively within the scope of this study. This is a multicentre registry, where each referring centre records the required patient data in an electronic case report form, managed by CTCM. Each participating centre has a designated local principal investigator responsible for overseeing the data collection process.

### **9.2 Amendments**

An amendment to the SMILE registry protocol was submitted on July 5, 2022, to the Medical Ethics Review Committee of Maastricht UMC+. This amendment proposed the implementation of a no-objection system for patient inclusion, replacing the requirement for written informed consent. The change was necessary to ensure the feasibility and comprehensiveness of patient recruitment since the original consent procedure limited the inclusion rate and the registry's value. The amendment was approved after submission, ensuring compliance with ethical and legal guidelines while enabling the collection of essential data to improve care for MR patients.

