## **2 Objectives**

### **2.1 Primary objective**

To evaluate the co-primary clinical endpoints during a five-year follow-up:

- all-cause mortality
- heart failure hospitalisations

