### **4.4 Sample size**

There will be no predefined endpoint for patient inclusion. The register strives to enrol all patients who meet the criteria for moderate-severe MR, as determined by echocardiography, from the designated participating centres. These patients will be registered at the four participating hospitals and followed up for a period of five years.

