### **5.7 Feasibility of the recruitment schedule**

The recruitment for the SMILE registry is designed to be feasible and efficient within the clinical workflow. Patients with moderate-severe MR are identified during routine echocardiographic examinations. These patients are subsequently contacted via post or telephone to inform them about the registry and their eligibility to participate. The use of an opt-out/no-objection system ensures that recruitment can proceed without the need for formal written consent, reducing delays and enabling the inclusion of nearly all eligible patients. This approach allows for a comprehensive and representative dataset while respecting patient autonomy and privacy.

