## 7 Statistical analyses

### 7.1 Baseline, primary, secondary outcomes

Analysis will begin with descriptive statistics to summarise baseline characteristics. Categorical variables will be presented as counts and percentages and compared using the Chi-square test. Ordinal variables will be reported as frequencies and compared using ordinal or non-parametric tests. Continuous variables will be presented as means ( $\pm$  standard deviations) or medians (interquartile ranges), depending on the distribution, and compared using the independent t-test for normally distributed data or the Mann–Whitney U test for non-normally distributed data.

Time-to-event outcomes, including all-cause mortality and time-to-first heart failure hospitalisation, will be analysed using Kaplan–Meier estimates and compared using the log-rank test. Associations between baseline characteristics and clinical outcomes will be evaluated using multivariable Cox proportional hazards regression models, with results presented as hazard ratios (HRs) and 95% confidence intervals (CIs). A minimum of 10 events per variable will be considered to ensure statistical robustness.

Longitudinal changes in echocardiographic parameters and HRQoL will be analysed using mixed-effects models to account for repeated measurements within patients. MR severity will be demonstrated as an ordinal outcome, while continuous echocardiographic measures and HRQoL outcomes will be analysed using linear mixed-effects models. Treatment success will be evaluated using responder-based analyses based on annual follow-up assessments, and predictors of treatment success will be analysed using multivariable logistic regression models, with results presented as odds ratios (ORs) and 95% CIs. Analyses will be stratified by MR aetiology and, where appropriate, by management strategy (conservative, catheter-based, or surgical). Missing data will not be imputed; primary analyses will be conducted using all available data, with sensitivity analyses performed in complete-case cohorts. Statistical significance will be set as a two-sided  $p$ -value  $< 0.05$ .

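### Section 7.1 has no factor for the change from written consent to no-objection, so pooled five-year estimates may be biased, in either direction, if prognosis differs between the two regimes

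*Protocol*

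**What the plan says.** Protocol section 9.2 records the change: "An amendment to the SMILE registry protocol was submitted on July 5, 2022", introducing a no-objection system and "replacing the requirement for written informed consent". The reason given is that "the original consent procedure limited the inclusion rate". The effective date is not stated, only that "The amendment was approved after submission". The synopsis gives study initiation as 01-12-2020, read here as 1 December 2020.

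Section 2.1 sets the horizon: "To evaluate the co-primary clinical endpoints during a five-year follow-up". Section 4.4 has no end to inclusion, and each patient is "followed up for a period of five years". Section 7.1 analyses both co-primary endpoints by Kaplan–Meier and log-rank on all available data, and "Associations between baseline characteristics and clinical outcomes will be evaluated using multivariable Cox proportional hazards regression models". The stratification it names is MR aetiology and, where appropriate, management strategy. Consent regime is not mentioned.

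Of opt-out recruitment, section 5.7 says: "This approach allows for a comprehensive and representative dataset while respecting patient autonomy and privacy". Section 8.2 calls data collection under no-objection unbiased. Neither section says that patients enrolled before the change fall outside that description.

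**The concern.** By the protocol's own account, patients entered through two different selection mechanisms, and the first admitted fewer of those eligible. Enrolment date determines both the consent regime and how long a patient can have been followed at any data cut. Kaplan–Meier assumes that patients censored at a given time have the same future risk as those still observed. If prognosis differs by regime, administrative censoring in a pooled curve breaks that assumption: recently enrolled no-objection patients leave the risk set early, and the later intervals are estimated increasingly from consent-era patients.

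Both co-primary endpoints are evaluated over five years, which is where this imbalance is greatest. A five-year figure from a pooled curve could then describe neither regime, while being presented alongside wording that suggests a representative cohort. The same argument applies to time to first heart failure hospitalisation. The calculation below covers mortality only.

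**Working it through.** The protocol states no sample size, event count or five-year risk, so there is no figure of its own to reproduce.

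**Dates (from the protocol)**
- Consent era: 1 December 2020 to 5 July 2022 = 581 days = 581/365.25 = 1.591 years = 19.1 months. This is a minimum, since 5 July 2022 is the submission date.
- First possible five-year completion: 1 December 2025.
- First possible no-objection completion: 5 July 2022 + 5 years = 5 July 2027. Approval delay would make it later; retrospective inclusion under no-objection could make it earlier.

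**Model (assumptions, not protocol figures)**
- Uniform accrual within each era, with no-objection accrual r = 2 or 3 times the consent-era rate.
- No-objection inclusion starts on 5 July 2022.
- Constant hazards h = −ln(1 − p)/5, where p is the five-year risk in that era.
- Administrative censoring only.

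Let c = 1.591 and let A be the years from initiation to data cut. At follow-up time t:
- Consent-era patients with potential follow-up of at least t: n_C = min(c, A − t).
- No-objection patients: n_O = r × max(0, A − t − c).
- Consent-era share of the risk set: w(t) = n_C·exp(−h_C·t) / [n_C·exp(−h_C·t) + n_O·exp(−h_O·t)].
- Pooled five-year risk: 1 − exp(−∫₀⁵ [w·h_C + (1 − w)·h_O] dt).
- Target, the risk for all enrolled: [c·p_C + r(A − c)·p_O] / [c + r(A − c)].

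**Worked case:** January 2026, 30% versus 40%, r = 2.
- A = 1857/365.25 = 5.084, and r(A − c) = 2 × 3.493 ≈ 6.987.
- Target = (1.591 × 0.30 + 6.987 × 0.40)/8.578 = 38.1%.
- Consent-era share at year 0 = 1.591/8.578 = 18.5%. From year A − c = 3.5 onward it is 100%.
- Pooled Kaplan–Meier = 34.4%, which is 3.7 points too low.

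**Pooled estimate versus target (ranges over r = 2 and 3)**

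| Data cut | 30% vs 40%: pooled / target | 25% vs 45%: pooled / target | Points too low |
|---|---|---|---|
| Jan 2026 | 34.4–35.0 / 38.1–38.7 | 34.1–35.2 / 41.3–42.4 | 3.7–7.2 |
| Jan 2027 | 36.0–36.7 / 38.5–38.9 | 37.2–38.4 / 42.0–42.9 | 2.3–4.8 |
| Jan 2028 | 37.5–38.1 / 38.7–39.1 | 39.9–41.2 / 42.5–43.2 | 1.0–2.5 |
| Dec 2030 | 38.7–39.1 / 39.1–39.4 | 42.5–43.2 / 43.3–43.8 | 0.3–0.8 |

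The part of the curve resting on consent-era patients alone starts at about year 3.5 in January 2026 and year 4.5 in January 2027. In July 2027 (30% versus 40%, r = 2) their share is still 47% at year 4 against 14% at year 0, so some error persists after that date.

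**Other assumed risks, January 2026**
- 35% versus 35%: no error, at this or any date.
- 30% versus 32%: about 0.8 points too low.
- 40% versus 30%: about 4 points too high.

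**The case against.** The strongest reply is that both the existence and the direction of bias are assumed. Section 9.2 says written consent reduced inclusion; it does not say that inclusion depended on prognosis. The protocol gives no inclusion rates, baseline comparison or outcomes by regime. This stands, and it makes the point conditional. A reader might infer that the five-year results are wrong, or probably too favourable. The documents support neither.

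A reader might also infer that before mid-2027 the primary estimates come only from consent-era patients because only they have completed five years. That does not follow. Kaplan–Meier uses all available data, so no-objection patients contribute to the earlier intervals, and only the last part of the curve lacks them.

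No analysis date is fixed and the registry runs for at least ten years, so the largest figures apply only if five-year results are reported early. This also stands.

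Sections 5.7 and 8.2 can fairly be read as describing the current recruitment method rather than the whole dataset. On that reading a clarifying clause is enough, but it is still needed, because nothing separates the earlier patients.

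Finally, pooling is inferred from silence, and an analysis plan not seen here could add a regime factor. That weakens the point without removing it: the protocol itself names its stratification factors, makes the representativeness statements and records the change that qualifies them.

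**Conclusion.** The point holds in conditional form. One registry contains two selection mechanisms, section 7.1 does not separate them, and the representativeness wording is not limited to the second. Without retrospective inclusion, any five-year analysis before July 2027 has a tail estimated from consent-era patients alone.

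Whether this biases the estimates depends on a prognostic difference that the protocol neither shows nor excludes. Under assumed gaps of 10 to 20 percentage points, with consent-era patients at lower risk and no-objection accrual 2–3 times faster, the pooled five-year mortality is too low by about 4–7 points in January 2026. This falls to under 1 point by December 2030. The error disappears with equal risks and changes sign if consent-era patients are at higher risk. This is a worthwhile, inexpensive improvement, not a demonstrated error in the primary result.

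**What to change.** In section 7.1:
- Define consent regime by the date on which no-objection inclusion actually started, and state that date. State also whether patients seen before it were later included under no-objection; if so, classify them by the regime under which they entered.
- Stratify the log-rank and Cox analyses by regime.
- Present the co-primary five-year estimates by regime, with a sensitivity analysis restricted to no-objection patients. Stratifying the tests alone would not correct a pooled Kaplan–Meier curve.
- Compare baseline characteristics by regime, so that the assumption of similar prognosis can be examined.

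In sections 5.7 and 8.2, limit the statements on representativeness and absence of bias to patients included under no-objection.

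The cost is one derived variable, a few extra tables and some wording; no new data collection is needed beyond the enrolment date and the regime of entry. The downside is that the no-objection five-year estimate becomes available only from about mid-2027.

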## **10 Risk analysis**

This observational study follows standard clinical care protocols, and no additional invasive procedures or treatments are required for participants. All data collection is based on routine clinical evaluations, including echocardiography and annual follow-up visits. Participants are asked to complete a standardised SF-36 questionnaire annually, which is non-invasive and estimated to take approximately 15 minutes.

The primary risk associated with the study is the minimal burden of time and effort required to complete the annual questionnaire and attend follow-up visits. The collection of clinical data from medical records does not introduce any physical risk to participants. Given the observational nature of this study, no additional risks are introduced to participants beyond those inherent to standard clinical care.

## **11 Endpoint definitions**

### **11.1 Clinical endpoints (Primary)**

The primary clinical endpoints are all-cause mortality and time-to-first heart failure hospitalisation during long-term follow-up. Mortality and hospitalisation events will be collected during annual follow-up and, when applicable, verified through medical records with corresponding dates recorded.

### **11.2 Disease-specific endpoints (Secondary)**

MR disease progression will be assessed using longitudinal echocardiographic evaluations performed during routine clinical care. MR severity will be assessed according to guideline-recommended criteria at the time of analysis. MR progression will be defined as an increase of at least one MR grade compared with baseline.

In addition, left ventricular (LV) and left atrial (LA) remodelling will be assessed longitudinally using echocardiographic parameters. LV remodelling will be evaluated using LV end-diastolic diameter (LVEDD) and left ventricular ejection fraction (LVEF), while LA remodelling will be evaluated using LA volume index (LAVi). For clinical interpretability, remodelling severity will additionally be categorised based on guideline-recommended cut-off values at the time of assessment. For patients already in the most severe category at baseline, progression will be defined as a relative change of  $\geq 10\%$  from baseline.

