### **4.2 Inclusion Criteria**

All patients aged 18 years and older with moderate-severe MR as determined by echocardiography.

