#### **11.4 Treatment success (Secondary)**

Treatment success will be evaluated using responder-based analyses derived from annual follow-up assessments. For patients undergoing mitral valve intervention, treatment success will be defined as the first follow-up assessment at which MR severity is  $\leq 2$ , in combination with improvement in symptom burden ( $\geq 1$  NYHA class) and/or improvement in HRQoL (SF-36 increase  $\geq 5$  points) compared with baseline. For patients managed conservatively, treatment success will be defined as clinical stability, characterised by the absence of heart failure hospitalisation or mitral valve intervention during follow-up, together with non-worsening MR severity and stable or improved symptoms and/or HRQoL. LV and LA remodelling parameters will be analysed as longitudinal outcomes but will not be used as sole determinants of treatment success.

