|                                                                    | Aetiology                                 | Categorical | Primary, Secondary                                                         |
|                                                                    | Flail leaflet                             | Categorical | Yes, no                                                                    |
|                                                                    | Involved segment in mitral valve prolapse | Categorical | P1, P2, P3, A1, A2, A3, Posteromedial commissure, Anterolateral commissure |

|                            |                               |             |                                                                                                |
|----------------------------|-------------------------------|-------------|------------------------------------------------------------------------------------------------|
|                            | Severity of MI                | Categorical | Mild (Grade I), Mild to moderate (Grade II), Moderate to severe (Grade III), Severe (Grade IV) |
|                            | ERO                           | Numeric     | Effective regurgitant orifice                                                                  |
|                            | LAVi                          | Numeric     | Left atrial volume index                                                                       |
|                            | Regurgitant volume            | Numeric     | Volume of regurgitation                                                                        |
|                            | E/A ratio                     | Numeric     | Ratio of E-wave to A-wave                                                                      |
|                            | Maximum E-wave velocity       | Numeric     | Maximum velocity of E-wave                                                                     |
|                            | Vena contracta                | Numeric     | Diameter of vena contracta                                                                     |
|                            | PISA radius                   | Numeric     | Proximal Isovelocity Surface Area                                                              |

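### A one-grade rise cannot occur in patients who enter at Grade IV, and the protocol gives MR grade no rule for them

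*Protocol*

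**What the plan says.** Protocol Section 11.2 fixes the endpoint: "MR progression will be defined as an increase of at least one MR grade compared with baseline". The severity item in the Section 13 appendix has four levels: "Mild (Grade I), Mild to moderate (Grade II), Moderate to severe (Grade III), Severe (Grade IV"). There is nothing above the last.

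Section 4.2 sets entry as "All patients aged 18 years and older with moderate-severe MR as determined by echocardiography". The appendix attaches that term to Grade III and lists severe disease separately as Grade IV.

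The second paragraph of Section 11.2 deals with remodelling, measured by LVEDD, LVEF and LAVi. It closes with a ceiling rule: "For patients already in the most severe category at baseline, progression will be defined as a relative change of" at least 10% from baseline. The paragraph on MR grade has no such rule.

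Section 11.4 defines success under conservative management as "the absence of heart failure hospitalisation or mitral valve intervention during follow-up", "together with non-worsening MR severity and stable or improved symptoms and/or HRQoL". Non-worsening is not defined separately. Section 7.1 models predictors of treatment success by logistic regression, and Section 2.2 names both MR progression and predictors of success as secondary objectives. Section 1 adds predictors of MR progression as an aim of the registry.

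**The concern.** An endpoint defined as a step up a bounded scale is undefined for anyone already on the top step. If such patients are enrolled and counted, three things follow:

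- The overall progression rate depends on the baseline case mix as well as on the disease. Two centres or aetiology groups with the same behaviour below Grade IV would report different rates if their Grade IV shares differ.
- In any model of predictors of progression, baseline Grade IV has no events and looks perfectly protective. Covariates that track severity, such as EROA or regurgitant volume, are pulled the same way.
- If non-worsening in Section 11.4 is read as no rise in grade, conservatively managed Grade IV patients pass that component whatever happens to their valve.

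Section 11 is where the protocol fixes its endpoint definitions. The objection is therefore to a rule that is stated, not to detail that could be left to an analysis plan.

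**Working it through.** The protocol gives no progression rate and no grade distribution, so there is no figure of its own to reproduce. The check is logical, followed by an illustration on assumed inputs.

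**Step 1: can the event occur at Grade IV?** The event needs a follow-up grade of at least baseline + 1 (Section 11.2). The maximum grade is IV (Section 13). For baseline IV, IV + 1 is not a category, so P(progression | Grade IV) = 0.

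**Step 2: does the 10% rule fill the gap?** It stands at the end of the remodelling paragraph, after three continuous measures and their severity categories. Applied to a grade of 4, a 10% change would be 0.4 of a grade, which the scale cannot record. MR grade therefore has no ceiling rule.

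**Step 3: which grades are enrolled?**
- If Grade III only, every patient can progress and there is no dilution.
- If Grades III and IV, the only possible progression from entry is III to IV, and Grade IV patients add to the denominator only.

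Sections 4.2 and 13 do not settle which applies.

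**Step 4: size of the dilution.** Let s be the share at Grade IV at baseline and p the Grade III-to-IV risk. Both are assumed. Reported rate = (1 − s) × p.

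| p | s = 0 | s = 20% | s = 40% | s = 60% |
|---|---|---|---|---|
| 10% | 10% | 8% | 6% | 4% |
| 20% | 20% | 16% | 12% | 8% |
| 30% | 30% | 24% | 18% | 12% |

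For example, 0.30 × (1 − 0.20) = 0.24, 0.30 × (1 − 0.40) = 0.18 and 0.30 × (1 − 0.60) = 0.12.

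**Step 5: conservative success.** Let q3 and q4 be the probabilities that the other components are met in Grade III and Grade IV. Both are assumed, and meeting them is taken as independent of worsening in grade. Success is q3 × (1 − p) in Grade III and q4 in Grade IV, because the MR component is always met there. The odds ratio compares Grade IV with Grade III.

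| p | success, III (q3 = 50%) | OR if q4 = 50% | OR if q4 = 40% |
|---|---|---|---|
| 10% | 45% | 1.22 | 0.81 |
| 20% | 40% | 1.50 | 1.00 |
| 30% | 35% | 1.86 | 1.24 |

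At p = 20% and q4 = 50%, the odds are 0.50/0.50 = 1.00 against 0.40/0.60 = 0.667, a ratio of 1.50. If Grade IV could worsen at the same 20%, the ratio would be 1.00 with q4 = 50%. With q4 = 40% it would be (0.32/0.68)/(0.40/0.60) = 0.71 instead of 1.00. The ceiling pushes the ratio upward in each case, but where it ends up depends on q3 and q4.

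**The case against.** The strongest reply is that the problem may not exist. If moderate-severe means Grade III only, nobody enters at the ceiling and the dilution is zero. This stands as a condition on the finding. It does not dispose of it, because the protocol leaves the point open in its only clinical inclusion criterion.

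A second reply is that the progression objective does not rest on the grade rise alone. Section 7.1 treats MR severity as an ordinal outcome and plans linear mixed models for continuous echocardiographic measures, and EROA and regurgitant volume are collected. This softens the consequences. The progression endpoint itself is still the one-grade rise.

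A third reply concerns treatment success. A reader might infer that Grade IV patients under conservative care succeed automatically, or that Grade IV will emerge as a predictor of success. The text does not support that. They must also avoid heart failure hospitalisation and mitral valve intervention and have stable or improved symptoms and/or HRQoL. If they meet those requirements less often, the odds ratio can be 1.00 or below, as the working shows.

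A reader might also infer that repair or replacement erases progression by lowering the grade. The protocol does not say so. A rise seen before a procedure still meets Section 11.2, which is not tied to a final assessment. Interventions are recorded (Section 5.1), and analyses are stratified, "where appropriate, by management strategy (conservative, catheter-based, or surgical"). Intervention is itself a failure of conservative success, so it cannot create non-worsening there. How echocardiograms after a procedure count is not stated, and that may properly sit in the SAP. It forms no part of this point.

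**Conclusion.** The point holds in a conditional form. It is certain that the grade-rise definition gives a Grade IV patient zero chance of progression and that the 10% rule does not cover MR grade. It is conditional on Grade IV patients being enrolled that the overall progression rate is understated by the factor (1 − s) and that baseline severity looks protective against progression. The fall from 30% to between 24% and 12% rests on an assumed risk and assumed shares of 20% to 60%. The protocol supplies neither, and the effect is nil if only Grade III is enrolled.

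The effect on conservative success needs the further assumption that non-worsening means no rise in grade. One component is then automatic for Grade IV, and the net effect on predictors of success is not known. These are secondary endpoints, so the change should be made but does not touch the co-primary outcomes.

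**What to change.** 1. In Section 4.2, state whether entry is Grade III only or Grades III and IV, and reconcile the wording with the appendix labels.
2. In Section 11.2, limit the grade-progression endpoint, and any model of its predictors, to patients below Grade IV at baseline.
3. For patients at Grade IV at baseline, assess progression in Section 11.2 and non-worsening in Section 11.4 by a prespecified change in a quantitative measure already collected (EROA or regurgitant volume). Alternatively, for Section 11.4, report conservative success separately by baseline grade.

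The cost is wording in three sections and no new data items. There are two downsides. The grade-progression denominator becomes smaller. Echocardiography is routine care and Section 7.1 rules out imputation, so Grade IV patients without a quantified EROA or regurgitant volume would be lost from the quantitative assessment. If only Grade III is enrolled, item 1 is enough for the baseline ceiling.
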